### Study design

The Parkin’Play study is a multicenter phase-II open-randomized controlled study that aims to recruit 222 patients with Parkinson’s disease with PD-MCI. Patients are randomly assigned to the intervention (cognitive training) or the control group (waiting list). All participants will undergo three assessments (t = 0, t = 1, and t = 2), which consist of neuropsychological assessments and questionnaires. In 20 patients from each group (total *n* = 40) two fMRI scans will be obtained (t = 0 and t = 1). The duration of the main intervention will be 12 weeks. In order to investigate the compliance and attractiveness of the health game, patients will be given the opportunity to continue playing for an additional 12 weeks (Fig. 1). The study will be analysed based on an intention-to-treat approach and results will be published on behalf of the Parkin’Play investigators.

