**Fig. 2 Fig2:**
[figure not shown]
Feedback loops regulating the difficulty and pace of the AquaSnap training

The duration of the cognitive training period is set at 12 weeks with a cumulative duration of 18 h, divided over 36 sessions. In other cognitive training studies, the mean cumulative duration was 17,6 h with a range between 5 and 42 h and the mean training period was 9 weeks with a range between 4 and 24 weeks [10, 11, 24–26].

Time spent per day on gaming will be recorded automatically. There will no pre-set time limits in order to investigate the attractiveness of the games as well as the possibility of testing for addictive behaviour in post-hoc analyses. To prevent attrition due to an inadequate level of difficulty (i.e. too high or too low), coaches will contact the patients every two weeks in the first month to adjust the levels accordingly.

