#### Waiting list (control group)

The control group is designed as a waiting list group in order to increase compliance. The participants are required to perform the MyCQ™ assessment monthly. For motivational purposes, the control group is offered to take part in a deferred intervention after 12 weeks (e.g. from week 12 until 24), with the same intensity as the intervention group in the first 12 weeks.

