### Statistical analysis procedure

Differences between the intervention and control group in global cognitive function (compound score of the neuropsychological test battery) at 12 weeks (primary endpoint) will be compared using independent sample t-tests. In addition, differences between groups in the individual cognitive domains will be tested using multivariate analysis of variance (MANOVA). Change in cognition over time (baseline, 12 weeks, 24 weeks) will be tested using repeated-measures ANOVA. All tests will be two-tailed with alpha set at 0.05. The assumptions of normality and homogeneity of variance will be assessed by inspection of normal probability plots and residual plots. In case assumptions are not met, appropriate data transformations will be used. Secondary outcomes will be presented as means, standard deviations, minimum, maximum, median, lower and upper quartiles. The number of observations and changes from baseline will be presented. Categorical data will be presented in contingency tables as frequencies and percentages. The analyses will be performed on an intention-to-treat basis. A secondary “Per-Protocol” analysis will also be included for the patients who have fully completed the study protocol for the primary endpoint. In order to investigate the effect of ‘missingness’, sensitivity analyses will be performed, including missing data augmentation using multiple imputation by chained equations [45] and maximum likelihood estimation with random effects.

For the main study, interim analysis will be conducted after 40 patients have completed the 12-week cognitive training period, including the corresponding assessments, to find out if the training is particularly beneficial or not. If, after interim analysis, it can be concluded that the training is particularly harmful, we may end the study and analyze the study data. This will only be decided in consultation with the local ethics committee.

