### Power and sample size estimate

The Parkin’Play study is powered to show a moderate effect of the AquaSnap cognitive training on the standard neuropsychological assessment. A study in healthy older participants compared a brain training program (Brain Age) to a control condition (Tetris gaming) and found an ANCOVA-based effect size of Cohen’s f = 0.39 (eta^2^ = 0.13) on the Trail Making Test, which assesses cognitive flexibility, often reduced in PD [9]. This reflects a moderate-to-large effect size (equivalent of Cohen’s d of 0.78). The present population includes participants aged between 40 and 75 years old, but with PD. Still, we expect a moderate effect size (0.4–0.5). Therefore, the estimated sample size for detecting a difference between the means of the treatment groups on the compound score of standard neuropsychological tests, with a power of 0.8 and a Cohen’s d = 0.4, at an alpha-level of 0.05, for a two-sided test, and an allocation ratio of 1:1 is 200 patients.

Based on previous cognition training and video game clinical trials the attrition rate is estimated at 10 %, which yields an additional 22 patients that should be recruited for participation [9, 11, 50]. This leaves a total of 222 patients that should be recruited.

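### The analyses called intention-to-treat leave out randomised patients without scores: the primary t-test needs a 12-week score and ignores baseline, and the methods that use all available data are only sensitivity analyses

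*Protocol article*

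**What the plan says.** The Protocol article promises intention-to-treat twice. Study design states "The study will be analysed based on an intention-to-treat approach", and Statistical analysis procedure states "The analyses will be performed on an intention-to-treat basis".

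Statistical analysis procedure then fixes the methods. The compound neuropsychological score "at 12 weeks (primary endpoint) will be compared using independent sample t-tests". For the longitudinal question, "Change in cognition over time (baseline, 12 weeks, 24 weeks) will be tested using repeated-measures ANOVA". No imputation and no baseline term is attached to the t-test. To study the effect of missing data, "sensitivity analyses will be performed, including missing data augmentation using multiple imputation by chained equations", together with maximum likelihood with random effects. A separate per-protocol analysis covers patients who completed the protocol.

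Power and sample size estimate sizes the comparison at 200 patients. It says "the attrition rate is estimated at" 10% and adds 22 patients, for a total of 222. Drop-outs and adverse events says only that patients who drop out are encouraged to attend follow-up.

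Cognitive training (intervention group) treats game difficulty as a possible cause of loss: coaches contact patients "To prevent attrition due to an inadequate level of difficulty (i.e. too high or too low". Waiting list (control group) gives controls no game in the first 12 weeks. For that arm, "The participants are required to perform the" monthly MyCQ assessment, and the game is offered from week 12.

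**The concern.** A t-test on 12-week scores cannot include a patient who has no 12-week score. Because baseline is not in the model, what is known about that patient at entry is also unused. Classical repeated-measures ANOVA goes further: a patient seen at baseline and week 12 but not at week 24 is lost altogether, and this is the test that bears on the secondary objective of persistence. The methods that use the data of all randomised patients are already named, but only in a supporting role.

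This matters if loss is related to cognition in a way that differs between arms. That is plausible here: the trial is open, only the intervention arm plays in weeks 0 to 12, and the document itself links attrition to game difficulty. The headline result would then compare two differently selected groups. In their standard form, both sensitivity methods assume that scores are missing at random given the data in the model, so agreement between them is no test of that assumption.

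**Working it through.** **1. What the planned sample size implies.** Inputs from Power and sample size estimate: d = 0.4, two-sided alpha 0.05, power 0.80, 1:1 allocation, attrition 10%.

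- Normal approximation: n per arm = 2 × (1.960 + 0.842)² / 0.4² = 98.1, so 99 per arm (198 in total). The exact t-test solution is 99.08, so 100 per arm, 200 in total. The stated figure is reproduced.
- Attrition: 200 / 0.9 = 222.2, given as 222. This is also reproduced.
- t-test power is 0.80 with 100 per arm and 0.84 with all 111 per arm.

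The sample size is not in error. It shows that the stated 80% power belongs to an analysis of about 200 observed patients, so the plan itself allows for 222 − 200 = 22 randomised patients being absent from the primary comparison.

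**2. Bias of the observed-case t-test.** Let a be the share of an arm without a 12-week score, and k the gap in SD units between patients with a score and patients without (positive if those missing would have scored lower). The observed mean of an arm exceeds its full mean by a × k, so

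bias = a_I × k_I − a_C × k_C, with SE = √[1/(111(1 − a_I)) + 1/(111(1 − a_C))].

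With no true effect, the two-sided error is 1 − Φ(1.96 − bias/SE) + Φ(−1.96 − bias/SE).

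The arm split and k are **assumptions**, since the document gives neither. Overall loss is held at the planned 10%.

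Worked case, 15% intervention and 5% control, k = 0.5 in both arms:
- bias = (0.15 − 0.05) × 0.5 = 0.05 SD
- SE = √(1/94.35 + 1/105.45) = 0.142, so bias/SE = 0.353
- error = 1 − Φ(1.607) + Φ(−2.313) = 0.054 + 0.010 = 0.064

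| Loss, intervention / control | k (SD) | Bias (SD) | Type I error |
|---|---|---|---|
| 10% / 10% | same in both arms | 0 | 5.0% |
| 10% / 10% | 0.5, intervention arm only | 0.05 | 6.4% |
| 15% / 5% | 0.25 | 0.025 | 5.4% |
| 15% / 5% | 0.5 | 0.05 | 6.4% |
| 18% / 2% | 0.5 | 0.08 | 8.7% |
| 15% / 5% | 1.0 | 0.10 | 10.9% |
| 20% / 0% (extreme) | 1.0 | 0.20 | 29.0% |

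Reversing the sign of k, or the split between arms, reverses the sign of the bias and leaves the two-sided error unchanged. A bias of 0.05 SD is 0.05 / 0.4 = 12.5% of the planned effect.

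**3. What the sensitivity analyses can show.** Study activities schedules the battery at baseline, week 12 and week 24 in both arms, and the MyCQ also at weeks 4 and 8. If dropout depends on such observed data and the models include them, imputation and likelihood estimates should move away from the t-test and reveal the selection. If dropout depends on the unseen 12-week score itself, both can agree with each other and still be wrong.

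**The case against.** Several points on the other side are sound.

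- A reader might infer that the primary analysis is restricted to patients who completed training. It is not. Protocol completers form the separate per-protocol set, drop-outs are encouraged to attend, and anyone with a 12-week score is analysed as randomised. Stopping the game is not the same as a missing outcome.
- A reader might infer that the bias must favour the game, because weaker patients would give up. The Discussion does say that a task that is too hard may make patients stop, but Cognitive training (intervention group) names difficulty in both directions. A game that is too easy could lose stronger patients. The adaptive design and the coaching calls also reduce the risk.
- A reader might infer that nothing in the plan would expose selective dropout. That goes too far: selection on measured baseline cognition is the case that the planned imputation and likelihood analyses can handle.
- Dropout related to cognition does not by itself invalidate the comparison. With matching loss and matching gaps in the two arms, the bias is zero.
- The list of sensitivity analyses is open-ended, and imputation details may sit in a fuller document. The absence of a not-at-random analysis from the article is therefore no error in itself.

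What remains is what the article does fix: an unadjusted observed-case test as primary, an ANOVA that discards incomplete patients, and the more suitable methods in second place, all under an intention-to-treat label. Even where the sensitivity analyses would detect selection, the headline result would still be the affected one.

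**Conclusion.** The point holds in limited form. The intention-to-treat label does not fit the primary t-test or the repeated-measures ANOVA as far as patients without scores are concerned, about 22 of 222 at the planned attrition. For everyone with a 12-week score, analysis by randomised arm is preserved in the primary test.

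The likely size is modest. It ranges from zero, when loss and gap match across arms, to about 0.05 SD in either direction and a type I error of about 6.4% under the assumed 15%/5% split and 0.5 SD gap. It becomes large only if loss is both strongly unequal and strongly selective. The document supports neither a particular split nor a direction, so no claim of bias towards benefit can be made. The choice should be corrected because a better analysis is already at hand, not because the planned one is shown to fail.

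**What to change.** - Make the primary analysis a likelihood-based mixed model for repeated measures with arm-by-visit terms, baseline score, site and age group, taking the 12-week contrast as the primary estimate. It should include all randomised patients with the data they have. For patients with only a baseline score to contribute, baseline has to enter as a response with a common mean across arms rather than as a covariate. The alternative is a baseline-adjusted analysis of data multiply imputed within arm.
- State the missing-at-random assumption on which this rests.
- Use the same model in place of repeated-measures ANOVA for change to week 24.
- Keep the observed-case t-test as a supportive analysis.
- Add one delta-adjusted imputation, shifting the imputed scores stepwise in either direction to see when the conclusion changes. This is a cheap, optional check on the untestable assumption.
- If MyCQ scores serve as imputation predictors, use them within arm only, because Outcome measures says that the MyCQ is built into the game and does not measure the treatment effect independently.

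The cost is slightly more analysis work and a reordering of methods that are largely named already. No new data and no change in sample size are needed. Baseline adjustment should also improve precision, by an amount that depends on the correlation between baseline and 12-week scores, which the document does not give.

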### Study activities

Enrolment will take place in the weeks prior to baseline assessment, except for the additional inclusion assessments (see Table 4). The following demographics and general variables are collected at baseline: date of birth, sex, educational level, age at onset, disease duration, and details on Parkinson medication (i.e., drug name, dose, frequency, levodopa equivalence). Details on Parkinson medication will also be collected at both follow-up measurements. Randomization will be performed after the baseline assessment. Primary and additional outcome assessments will be performed at baseline, after 12 and after 24 weeks follow up. The additional fMRI scans will be performed at baseline and after 12 weeks, matching the primary outcome assessments. The intervention group will be required to play the health game from start of the intervention until week 12 for at least 36 sessions of 30 min (three times a week). After week 12, both the intervention as well as the control group will be allowed to continue playing the health game free of choice. All patients will be examined in their on-state.

**Table 4 Tab4:** Study schedule and assessments

	Timepoint →	-*t* _1_	*t* _0_			*t* _1_	*t* _2_
	Visit # →	0	1			2	3
	Week # →	-1 to -3	0	4	8	12	24
ENROLMENT: Screening & inclusion assessments							
Regular clinical intake		X					
Demographics		X					
Inclusion/exclusion		X					
National Adult Reading Task			X				
Montreal Cognitive Assessment			X				
Epworth Sleepiness			X				
Levodopa equivalent dose (LED)			X			X	X
ASSESSMENTS: Primary outcomes							
Standard neuropsychological battery			X			X	X
MyCQ™ assessment			X	X	X	X	X
Additional outcomes							
Motor function (UPDRS part III)			X			X	X
Self-report questionnaires			X			X	X
Parkinson Disease Questionnaire-39			X			X	X
Pre-Rasch-built Overall Disability Scale			X			X	X
fMRI exclusion criteria		X					
fMRI scan			X			X	
INTERVENTIONS							
Randomization			X				
Game playing (36 sessions of 30 min)			X	X	X	*X*	*X*

Only for subset of patients (*n* = 40)

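### If full completion includes the 36 sessions, the secondary per-protocol comparison is selected differently by arm and is no longer randomised, with a plausible but not certain bias towards benefit

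*Protocol article*

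**What the plan says.** The protocol article, Statistical analysis procedure, sets the main basis: "The analyses will be performed on an intention-to-treat basis". It then adds a secondary per-protocol analysis "for the patients who have fully completed the study protocol for the primary endpoint". It says no more about who belongs to that set. The only test named for the 12-week compound score is an independent-samples t-test, with no baseline covariate.

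What there is to complete differs by arm:

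- **Trained arm** (Study activities): "The intervention group will be required to play the health game from start of the intervention until week 12 for at least 36 sessions". The sessions last 30 minutes, and Cognitive training (intervention group) gives the total as 18 hours. That section also states: "Time spent per day on gaming will be recorded automatically".
- **Waiting-list arm** (Waiting list (control group)): "The participants are required to perform the MyCQ™ assessment monthly". Training is offered to this arm only after week 12.
- **Both arms**: the baseline and 12-week assessments, and no other cognitive therapy during the study (Study population). Stable medication is requested, but changes are allowed (Medication adjustments).

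**The concern.** A per-protocol comparison is a fair contrast only if the retained patients in the two arms would have had similar outcomes without treatment. Here one arm may be filtered by 18 hours of demanding home training and the other by a few short tests and a visit. Patients who finish the training may differ from those who do not in baseline cognition, motivation or disease burden. Randomisation does not balance the groups left after that filter, and a t-test on the 12-week score does not correct for the difference.

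The article names no other analysis of the effect in patients who actually train. A positive per-protocol result beside a null intention-to-treat result could be taken as evidence that the game works when played as intended, even if selection alone produced it.

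**Working it through.** **The plan's own figure.** For d = 0.4, two-sided alpha 0.05 and power 0.8, the normal formula gives 2 × (1.960 + 0.842)² / 0.4² = 98.1 per arm. The exact t-test gives 99.08, so 100 per arm and 200 in total, as stated. Allowing for 10% attrition, 200 / 0.9 = 222.2, against the stated 222. The sample size reproduces and does not depend on this point.

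**Inputs.** From the article: 100 evaluable patients per arm, d = 0.4, two-sided alpha 0.05 (2.5% in the direction of benefit), and an overall attrition of 10%, not split by arm. Not in the article, so assumed:

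- p, the share of trainees in the per-protocol set: 60-90%
- pc, the share of controls in the set: 95%
- r, the correlation of the tendency to complete with the 12-week compound score: 0.1-0.3

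The per-protocol test is taken to be the same unadjusted t-test, since no other is named.

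**Model.** There is no true effect. In each arm the patients with the highest latent tendency to complete are kept. With φ the standard normal density and z_p the normal quantile at p, the mean shift in an arm that keeps a share p is r × φ(z_p)/p. Hence

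bias = r × [φ(z_p)/p − φ(z_pc)/pc], in SDs of the compound score.

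The standard error is √(1/(100p) + 1/95), and the probability of a false significant benefit is P(Z > 1.96 − bias/SE).

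**Worked case, p = 0.7, pc = 0.95, r = 0.2.** φ(z_p)/p = 0.3477/0.7 = 0.497, and φ(z_pc)/pc = 0.1031/0.95 = 0.109. Bias = 0.2 × (0.497 − 0.109) = 0.078 SD. SE = √(1/70 + 1/95) = 0.158. The probability of a false benefit is 7.1% instead of 2.5%.

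**Range, pc = 0.95.** Bias in SD, with the probability of a false benefit in brackets:

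| Trainees kept | φ(z_p)/p | r = 0.1 | r = 0.2 | r = 0.3 |
|---|---|---|---|---|
| 90% | 0.195 | 0.01 (2.9%) | 0.02 (3.3%) | 0.03 (3.7%) |
| 80% | 0.350 | 0.02 (3.6%) | 0.05 (5.0%) | 0.07 (6.9%) |
| 70% | 0.497 | 0.04 (4.3%) | 0.08 (7.1%) | 0.12 (11.1%) |
| 60% | 0.644 | 0.05 (5.1%) | 0.11 (9.5%) | 0.16 (16.2%) |

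The worst corner is 0.16/0.4 = 40% of the design effect.

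**Where it vanishes or reverses.**

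- r = 0: the bias is zero at any completion rate.
- Equal completion with the same selection in both arms: zero.
- r = −0.2 at 70% against 95%: −0.08 SD.
- r = 0.2 with 90% of trainees and 80% of controls kept: 0.2 × (0.195 − 0.350) = −0.03 SD.

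**The case against.** The strongest reply is that this is a conventional secondary analysis. Intention-to-treat is already the main basis, nothing in the article lets the per-protocol result decide anything, and its detailed definition may properly sit in a full protocol or analysis plan that is not shown. That stands as far as it goes. The lack of a definition is not the point, and the weight of the point is small. But more detail would not cure the asymmetry unless the session requirement were dropped, and then the set would say nothing about patients who trained.

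The wording is also open. Full completion for the primary endpoint could mean only the assessments up to week 12. The 36-session reading is the natural one because Study activities makes the sessions a requirement, but it is a reading, so the point is conditional on it.

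A reader might go further and infer that only the trained arm can fail the protocol, that nearly all controls stay in, and that the result is therefore biased towards benefit. The documents do not support this:

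- Controls can fail the monthly online test, the 12-week visit or the bar on other cognitive therapy. Only the session requirement is confined to the trained arm.
- No completion rate for controls is given. The statement "The control group is designed as a waiting list group in order to increase compliance" gives a reason for the design, not a rate, and the 95% used above is an assumption.
- The sign is not settled. The Discussion says that too hard a task may make patients stop playing, which points to loss of weaker patients. But Cognitive training (intervention group) names difficulty that is too high or too low as a cause of attrition. The adaptive difficulty and the coach contacts in the first month should also weaken any link between ability and adherence.

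**Conclusion.** The point holds in conditional form, as a minor one. If full completion includes the 36 sessions, the per-protocol set is selected on behaviour after randomisation that differs by arm, and the unadjusted comparison is not protected by randomisation. Bias towards benefit is plausible, not certain. Its size, about 0.01 to 0.16 SD, rests wholly on assumed completion and correlation. At 90% against 95% completion it is at most 0.03 SD, which is negligible. At 60% with a correlation of 0.3 it is large enough to mislead. The intention-to-treat analysis and the sample size are unaffected.

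**What to change.** 1. Label the per-protocol result descriptive and non-randomised, and adjust it for the baseline compound score. Adjustment removes imbalance on that score but not on motivation or other unmeasured factors.
2. For the effect of training itself, add a complier-average (instrumental-variable) estimate, with randomisation as the instrument, logged hours played (or any playing) to week 12 as the exposure, and the baseline compound score as covariate. The design suits this: controls are offered training only after week 12, playing time is logged automatically, and Drop-outs and adverse events says that patients who drop out are encouraged to complete follow-up, so outcomes in non-adherers should often be available.
3. Do not use a 36-session cut-off as the exposure. It credits the whole effect to those who reach the cut-off. If partial training also works, an intention-to-treat effect of 0.40 with 70% reaching 36 sessions would become 0.40/0.70 = 0.57.

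The cost is a short addition to the analysis plan and no new data. The downsides are a wider interval and the assumption that allocation acts only through playing and, when hours are used, roughly in proportion to them. Coach contacts and open allocation could breach the first assumption, so it should be stated with the result.
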